### **7.5 Statistical Procedures for Analysis of Acceptability Data**

There will be 36 participants in the study divided in three different experimental conditions (2 gel arms and one placebo arm) with 12 participants each. The quantitative acceptability assessments will consist of one Baseline Behavioral Questionnaire (BBQ) filled in once by all 36 participants, and one Product Acceptability questionnaire (PAQ) filled in once by all participants after Treatment Stage 2. The qualitative in-depth questionnaire will be conducted by phone after visit 5.

In terms of the quantitative data, our main prediction is that after one week of practice in the use of the product, respondents will, on average, report high intentionality to use the product in the future every time they have receptive anal intercourse. Furthermore, participants will report high intentionality to use the product in those occasions when they don't use condoms. High intentionality will be defined as an average score in the upper one third of the Likert scales measuring these intentions. Additionally, we anticipate that, even though many of the individuals who voluntarily enroll in a study like ours will be predisposed to like the product (as measured at baseline by the BBQ Intentions scale), we forecast that the experience of using the gel will on average increase their intentionality after experiencing the product. We do not anticipate differences in intentionality to use the product in the future among the three arms, since the placebo is designed to be quite similar to the UC-781 conditions.

The quantitative data will also provide descriptive statistics of acceptability of the product, the application process, applicator, as well as the degree to which participants were bothered by leakage, soiling, or other problems related to gel use. Descriptive statistics will also help us measure perceived possibility of covert use and willingness to use a higher volume than the one used in the study.

One of the drawbacks of quantitative assessments of microbicide acceptability is that this construct is unlikely to provide a static result that cannot be expected to be valid once and forever. One's willingness to use a product in the future may be affected by a number of interpersonal and contextual circumstances. To tackle this issue, we will rely on measures that are taken close to the end of the study, when participants have had sufficient practice occasions to achieve more stable opinions on what using the product will be like. Furthermore, taking advantage of the relatively small number of participants in the study, we will integrate quantitative and qualitative data closely so as to explore the roles that different factors play in acceptability and the meaning that enema and gel use as HIV-prevention tools ultimately have for the participants. For example, if in the BBQ a participant describes habitually having RAI using only saliva as a lubricant, and this may negatively influence the acceptability of a gel delivered intrarectally, we will be able to explore this issue in detail with the specific participant during in the in-depth interview that will take place after visit 5. This will give us the chance to explore ways to promote or enhance microbicide acceptability in such cases, and also it will elicit some new hypotheses that could be explored in future studies.

The in-depth interviews will be audio-taped, transcribed, and analyzed for content. In the initial stage of this qualitative data processing, two separate investigators will identify categories, themes, and patterns, and develop a coding scheme. Codes generated by the

two investigators will be compared and synthesized to end up with shared coding structure that will constitute the preliminary codebook. This codebook will be refined through further coding and discussion between the coders until consensus is reached. The analysis of coded material will lead to the progressive identification of categories, themes, and patterns. This will involve noting regularities in the setting or people under study and organizing them under a conceptual label. As the analysis progresses, hypotheses will be developed and challenged with the rest of the collected qualitative data. Ultimately, the insights gained from the qualitative data will be integrated with the results of the quantitative assessment with the purpose of creating a full-fledged picture of the different factors affecting acceptability.

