| H       | HIV Testing                      | By eligibility criteria, all participants will be HIV-negative. We will assess frequency of HIV testing and latest test occasion prior to enrollment in the study.                                                                                                                                                                                                                                                                                                                                                                                                                                      |
| I       | Rectal Microbicide Intentions    | To assess intentions to use a microbicide gel and a preparatory enema before RAI. This will allow us to detect pre-trial attitudes about such products and how they may affect later ratings.                                                                                                                                                                                                                                                                                                                                                                                                           |
| J       | Pleasure                         | Severy, et al.  stated that one of the main reasons people have sex is for pleasure. These items explore the effect of condoms on sexual pleasure. They will serve as baseline to compare pleasure ratings related to the different products used in the trials.                                                                                                                                                                                                                                                                                                              |

**Product Acceptability Questionnaire (PAQ)** The PAQ will be completed within the Visit 5 window after the completion of treatment stage 2, once the participant has had the opportunity to familiarize himself/herself with method of application, applicator, and product characteristics. The Product Acceptability Questionnaire includes both close-ended and open-ended questions (see Table 3)

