**Table 3: Product Acceptability Questionnaire (See Appendices VI a and VI b)**

| Section | Title:                                 | Content                                                                                                                                                                                         |
|---------|----------------------------------------|-------------------------------------------------------------------------------------------------------------------------------------------------------------------------------------------------|
| A       | PRODUCT ACCEPTABILITY                  | Likes and dislikes of physical characteristics of the product and sensations                                                                                                                    |
| B       | APPLICATION PROCESS                    | Ease of application, position, timing                                                                                                                                                           |
| C       | APPLICATOR                             | Likes and dislikes about applicator, its tip, and its portability                                                                                                                               |
| D       | CHANGES IN VOLUME USED                 | Any changes introduced by the user in the volume of product applied                                                                                                                             |
| E       | EXPERIENCES USING THE PRODUCT          | Leakage, soiling, or other product side effects, and how much the participant was bothered by them; feeling that the product was absorbed in the intestine                                      |
| J       | INTENTION TO USE PRODUCT IN THE FUTURE | Willingness to use a product that contributed to provide some protection against HIV; willingness to use it when condoms are not used, if wait period were required, and according to its cost. |
| K       | WILLINGNESS TO USE HIGHER VOLUME       | Attitudes about different product volumes                                                                                                                                                       |

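### Section 7.5 credits an uncontrolled before-to-after rise in intention to using the gel, and gives no UC-781-versus-placebo estimate for a versus-placebo objective

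*Protocol*

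**What the plan says.** Protocol 7.5 makes three statements about intention to use the product.

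- The main prediction is a high mean after the week of use, defined as an average in the top third of the Likert scales. It uses no baseline value.
- As an addition, it accepts that many volunteers "will be predisposed to like the product (as measured at baseline by the BBQ Intentions scale"), and continues: "we forecast that the experience of using the gel will on average increase their intentionality after experiencing the product".
- On the arms: "We do not anticipate differences in intentionality to use the product in the future among the three arms". The reason given is that the placebo closely resembles the UC-781 gels.

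The design is given as "2 gel arms and one placebo arm) with 12 participants each".

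In 2.1.1, Table 2 describes BBQ section I: "To assess intentions to use a microbicide gel and a preparatory enema before RAI". Its stated purpose is: "This will allow us to detect pre-trial attitudes about such products and how they may affect later ratings". Table 3 describes section J of the Product Acceptability Questionnaire (PAQ): "Willingness to use a product that contributed to provide some protection against HIV; willingness to use it when condoms are not used", followed by a waiting period and cost.

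The primary objective in 2.1.1 covers both safety and acceptability of the two UC-781 strengths, each set against placebo.

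**The concern.** The second statement is causal. It says that using the gel will raise intention, and the only evidence it calls on is the difference between two questionnaires completed weeks apart by the same people. No group goes without a gel. Anything that moves all participants upward between BBQ and PAQ would look the same as an effect of use: growing familiarity, contact with staff, or a question put differently.

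The change also says nothing about UC-781 in particular. On the protocol's own forecast of no arm difference, placebo users would show the same rise. The objective asks for UC-781 against placebo, and 7.5 attaches no between-arm estimate to it. At stake is a statement that experience of the product increases willingness to use it, in a first rectal study meant to guide further development.

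**Working it through.** Section 7.5 contains no alpha, power, SD or expected change, so there is no figure to reproduce. The check sets the texts side by side and then shows, under assumptions, how large the ambiguity and the imprecision could be.

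**1. What the change can identify.** Write the post-use score minus the baseline score as U + F + M + error. U is the effect of using a gel, F is familiarity and study attention, and M is any difference between the instruments. The mean change over 36 participants estimates U + F + M. Because all three arms use a gel, comparing arms does not isolate U either; it isolates the difference between formulations.

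**2. Whether the instruments match.** Table 2 (BBQ section I) names a gel and a preparatory enema. Table 3 (PAQ section J) names a product, use without condoms, waiting and cost, and no enema. The once-daily Stage 2 dosing described in 4.4 and 5.6 includes no enema step. So M need not be zero. The tables are summaries, however, and the items (Appendices VIa and VIb) are not shown.

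**3. Whether no arm difference can be presumed.** The expectation in 7.5 rests on a similar placebo. Section 4.2 describes these products:

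| | UC-781 gels | Control gel |
|---|---|---|
| Base | Carbomer 974P, methylcellulose, glycerin | Hydroxyethyl cellulose |
| Colour | Off-white to light yellow (0.1%); light yellow (0.25%) | Clear |
| pH | 5.2 | 4.4 |

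A difference in acceptability is therefore plausible enough to estimate.

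**4. Illustration of the before-after ambiguity.** Assumptions: n = 36, U = 0, a shared shift F + M = d SD, equal SDs, pre-post correlation r, and a two-sided 0.05 paired t-test with 35 df (critical value 2.030). The noncentrality is d × √36 / √(2(1 − r)). For d = 0.3 and r = 0.5 this is 0.3 × 6 / 1 = 1.8, and the probability of a significant rise is 0.417.

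| d (SD) | r = 0.3 | r = 0.5 | r = 0.7 |
|---|---|---|---|
| 0 | 0.025 | 0.025 | 0.025 |
| 0.2 | 0.165 | 0.214 | 0.325 |
| 0.3 | 0.315 | 0.417 | 0.618 |
| 0.5 | 0.693 | 0.831 | 0.964 |

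**5. Precision of the arm contrast.** In an ANCOVA with three arms and one covariate there are 36 − 4 = 32 residual df (t = 2.037). The standard error of one UC-781 arm minus placebo is √(1 − r²) × √(2/12).

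- r = 0.5: 0.866 × 0.408 = 0.354 SD, so the 95% half-width is about 0.72 SD.
- r = 0: 0.408 SD, so the half-width is about 0.83 SD.

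The difference detectable with 80% power is (1.960 + 0.842) × SE, about 0.99 SD at r = 0.5 and 1.14 SD at r = 0. For a true difference of 0.5 SD at r = 0.5, power is about 28% (noncentral t). The contrast is useful as an interval and weak as a test.

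**The case against.** The strongest reply is that this is a subsidiary forecast. The acceptability criterion is the post-use level, 7.5 says it will rely on measures taken near the end of the study, and the sentence itself concedes that volunteers may be favourable from the start. No test or reporting rule is attached, and such detail may sit in a statistical analysis plan that is not shown. All of that stands, and it limits the weight of the point. It does not repair the causal wording, which the protocol itself supplies.

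Four stronger readings are tempting, and the documents do not support them.

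- A reader might infer that any shared change will be reported as a gain in acceptability. Only an upward change could be, and nothing prescribes that report.
- A reader might take 21% to 83% as the plan's false-positive rate. These are probabilities for a paired test that the protocol does not name, under a shift assumed to be wholly unrelated to use.
- A reader might conclude that the two questionnaires ask different questions. That is visible only in one-line summaries. Section 7.5 mentions intention for every act of receptive anal intercourse, which the section J summary omits, so the summary is not a full list of items.
- A reader might expect a UC-781-versus-placebo contrast to rescue the forecast. It cannot: every arm uses a gel, and a rise under placebo is what the forecast predicts. The contrast answers the stated objective, which is a separate question.

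Nor are the arms ignored, since 7.5 states an expectation about them. What it lacks is an estimate, and the ground for the expectation sits badly with 4.2.

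**Conclusion.** The point holds in a limited form. The forecast rise is an uncontrolled before-after change, measured with intention sections that are summarised differently, and it should not be attributed to using the gel. Separately, an objective stated as UC-781 versus placebo has no between-arm estimate in 7.5, only an expectation of no difference that the control gel's description does not clearly support.

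No error of known size can be given. Over assumed shared shifts of 0.2 to 0.5 SD and correlations of 0.3 to 0.7, a significant pooled rise unrelated to gel use would occur with probability from about 0.17 to 0.96, if a paired t-test were the analysis. The upper-third criterion is untouched. The change is worth making before enrolment, because a baseline item that was not asked cannot be recovered later.

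**What to change.** In 7.5:

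1. Remove the attribution of the BBQ-to-PAQ change to the experience of using the gel. Report that change by arm, as descriptive, and only for items with the same content and response scale in both questionnaires. Confirm from Appendices VIa and VIb which items qualify; if none does, add one matched gel-only item.
2. To answer the stated objective, regress PAQ intention on arm (placebo as reference) and BBQ intention. Report each UC-781-minus-placebo difference with its 95% confidence interval. This is the baseline-adjusted model that 7.6 already sets out for continuous mucosal measures, and it gives the BBQ score the role Table 2 describes.

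The cost is a few sentences and at most one item in a web questionnaire that the trial is already programming. There are two drawbacks. The intervals will be wide, with a half-width of roughly 0.7 to 0.8 SD at 12 per arm for correlations of 0.5 down to 0, so a lack of difference must not be read as equivalence. Any item altered to match also slightly reduces comparability with the earlier acceptability study that supplied the instrument.

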## **7.6 Statistical Procedures for Analysis of Mucosal Damage Parameters**

The associations of six sets of mucosal parameters with the use of study product will be examined as a secondary objective. Four of these parameter sets (Histopathology, Cell Phenotype, Cytokine profile, Fecal Calprotectin) are collected three times per patient: at baseline, post-Treatment 1 and post-Treatment 2. The remaining two sets (Epithelial Sloughing and Immunoglobulins) are four times per patient: at baseline, pre- and post-Treatment 1, and post-Treatment 2. For all six parameter panels, the main question of interest is whether the three treatment groups (placebo, low, and high) have systematically different mucosal damage parameters post-Treatment 1 and post-Treatment 2. In particular, we will be assessing whether either of the UC-781 treatment groups have evidence of more mucosal damage than the placebo group. As described below, at least four of the six parameter sets should be stable and sensitive enough that important clinical differences would be statistically detectable.

As subjects will be randomized to the three treatment groups, systematic baseline differences are not expected; however, due to the relatively small study size, it is quite likely that many parameters will be quite different between treatment groups at baseline. All analyses will therefore be conducted both with and without controlling for baseline measurements. For continuous measures, it is well-known that controlling for baseline differences in regression models is more powerful than analyzing changes from baseline.

The basic model for analyzing continuous measures adjusting for baseline differences will be the analysis of covariance (ANCOVA) model regressing the continuous parameter at either post-Treatment 1 or post-Treatment 2 on the continuous baseline value and the categorical treatment group membership (with placebo as the reference group). The estimated regression coefficients for the treatment group will then be directly interpretable as the difference between low vs. placebo and high vs. placebo, post-Treatment 1 or post-Treatment 2 after adjusting for baseline differences. This model without the baseline values reduces to the simple one-way ANOVA model with treatment group as the predictor. For analyzing binary or ordinal measures, we will use the logistic regression version of these models. That is, we will regress the outcome post-Treatment 1 or post-Treatment 2 on group membership and on baseline value (when adjusting for baseline differences).

As we will be analyzing group differences in a large number of parameters, some attempt must be made to account for multiple hypothesis testing. We will address this multiple comparisons problem both informally and formally. Informally, particular group differences significant at the 0.05 level or smaller will be flagged as at least suggestive and those with extremely strong p-values (e.g. 0.001 or less) will be carefully examined. In addition, differences seen consistently for related parameters will carry more weight. Formally, we will apply corrections to the p-values. Of these, the Bonferroni method is the simplest, but also the weakest. We will employ the more powerful stepdown methods implemented in

the MULTTEST procedure in SAS v 9.1 (SAS Institute, Cary, NC).

We will also investigate longitudinal (three or four time points) and/or multivariate (simultaneous examination of multiple measures in a set) modeling techniques. The longitudinal analyses will most likely not be additionally informative, as there are only three time points for most of the parameters. Multivariate techniques are expected to result in potentially substantial power increases. Our previous studies with phenotype and cytokine panels have shown strong correlations between measures as well as good stability over time (i.e. high intrasubject correlations) in steady state for many of the measures. In this setting, for example, factors derived using principal components analysis would likely have stronger association with group membership than any one particular measure in the set. An additional strength of the longitudinal and multivariate approaches is that they provide an alternative solution to the multiple testing problem that arises with examining each timepoint and each parameter individually.

- Epithelial Sloughing

The simplest analysis for the epithelial sloughing measurements will look at the presence or absence of sloughing. Additionally, we may employ the five point ordinal scale of, which ranges from 0 (no evidence of sloughing) up to 4 (evidence in all four quadrants). For these data, there is baseline measurement will allow screening out of post-Treatment 1 false positives.

- Histopathology

As in the sloughing data, we will begin by examination of a two point (normal versus abnormal) or three point (normal, slightly abnormal, abnormal) scales. Based on initial analyses of the HPTN 056 histopathology panel data, we do not expect that quantitative measures will be substantially more informative than simple qualitative readings.

- Mucosal mononuclear cell phenotype

Many of the flow cytometry measurements from the HPTN 056 study are quite stable across time. Parameters with high intrasubject correlations (RFI measures are log-transformed) include %CD3, %CD4, %CD8, %CD31, CD38RFI on CD4+, CD38RFI on CD8+, %CD38|CD4, and %CD38|CD8 which have intrasubject correlations of between 0.7 and 0.9. Thus, we expect that clinically important differences in these parameters between treatment groups would be found to be statistically significant in our analyses. CCR5-related parameters had moderate stability (intrasubject correlations of around 0.5).

- Mucosal cytokine Profile

The cytokine data in HPTN 056 and earlier work of our group for RANTES, IFN- $\gamma$ , and IL-10 all showed strong stability (intrasubject correlations between 0.7 or 0.8; analysis is on log-transformed scale for all three of these). Again, this suggests that any clinically meaningful differences between treatment groups are likely to result in small p-values.

- Mucosal immunoglobulins

The immunoglobulin data collected in HPTN 056 appears to be moderately stable within subject (intrasubject correlations are between 0.3 and 0.5 for various measures of IgA and IgG).

- Fecal calprotectin

The fecal calprotectin marker has been shown to be extremely sensitive for discriminating several clinical conditions such as active and inactive Crohn's disease. The large majority of measurements for inactive subjects were below normal thresholds and nearly all measurements for active subjects were above normal thresholds. For our study, this suggests that this marker will be particularly helpful in detecting evidence of mucosal damage in the treatment groups.

